**Tracking Patients and Anonymization**

1. **Creating a unique anonymised study ID for each patient:**
   After a patient has given written consent and agreed to take part in this study, the local at the recruitment site will inform the project co-ordinator at the Sponsor site. The project co-ordinator will allocate each patient with a unique study ID. Both individuals (the project co-ordinator at the Sponsor site and the administrator at the local sites) will record the unique study ID against the patient’s clinical details (name, DOB, NHS number, hospital site from which they were recruited, local hospital number) on their respective study logs. This unique study ID is a 4 digit number pre-fixed by the Hospital ID and the patient’s initials e.g. NOH_JS_0001**.** See Table below for hospital site ID.
2. The study log will be held on a NHS computer at all participating sites. The office in which the computer holding the log is held is secure: the computer and the study folder file will be password-protected. Apart from the project co-ordinator and the local administrators, the only other persons who will hold these passwords will be the R&D managers on the various NHS Trust sites: this is in case anything were to happen to the project co-ordinator. This ensures that researchers and individuals how take blood including the clinical team are not able to link the Unique study ID with data and samples.

All paper documents containing patient identifiable data will be kept in lockable storage investigator sites.

1. **Sample ID, linking to unique patient ID and sample tracking**All samples will be labelled at the study sites with the patient’s unique study ID (for example NOH_JS_0001) in addition to the date the sample was taken. The local investigators will document on the study log that a sample has been taken and the date on which it was taken and the date it was posted to the Sponsor site. When the sample is put in the post the local administrator will send an email stating that a sample is to be expected.

On receipt of the sample at the Sponsor site, the researchers will log it onto Pro-Curo, an established commercially available auditable software programme, used for tracking and barcoding samples. Each sample ID will be allocated an ID by Pro-curo in an automated fashion and this sample ID will be linked to the unique study ID of the relevant patient. All samples will then be labelled with the unique study ID (for example RNOH_JS_0001) plus the Pro-curo sample ID, thereby ensuring that the samples are completely anonymised to the research and clinical staff. This is because the researchers will not be able to link the patient unique ID or the sample IDs to the patient’s name, date of birth, hospital number and NHS number.

**Site Codes for Generation of Unique Patients’ IDs**

| **NHS Trusts - Sites** | **Site Code** |
| --- | --- |
| Royal National Orthopaedic Hospital | RNOH |
| Nuffield Orthopaedic Hospital | NOH |
| Newcastle Upon Tyne NHS Trust | NUT |
| Robert Jones and Agnes Hunt Orthopaedic Hospital NHS Trust | OSW |
| Royal Orthopaedic Hospital NHS Foundation Trust | ROH |

# 4. ethical considerations

1. All information about participants and samples will be treated in the strictest confidence.
2. The team involved in the study is trained in information governance.
3. Patient samples will be pseudo-anonymised so that researchers will not have direct access to patients’ identifiable data (see example of Patient ID below)
4. Patient Data will be tracked on a secure NHS web-based system accessible by password and access granted by sponsor.
5. The data will be backed-up using the standard NHS system in our UKAS-accredited laboratory in case there is an IT failure. This back up system will be checked for robustness on a regular basis.

# 5. ADVERSE EVENTS

The collection of research blood samples does not constitute an intervention that involves the administration of any medication to the participant. Therefore the risk of a serious adverse event is small. However unexpected event such as breakage of a blood tube or a reaction to a skin dressing may occur. Specific risks are listed below.

1. **Complications as a result of Venepuncture**

It is possible a patient may develop a haematoma as a part of normal venepuncture procedure. The member of staff taking the blood sample will be trained and signed off in venepuncture, infection control and health and safety.

1. **Loss of sensitive patient data**

All members of the study will have undertaken training in information governance, good clinical practice and have knowledge of the human tissue act thereby reducing the risk of data loss.

## 5.1 REPORTING PROCEDURES

In the event of adverse events, investigations will be held by the principal investigator at the site where the incident took place via normal Trust adverse event reporting protocols.

All incidences will be documented in the site file and reported to the study sponsor and the Chief Investigator.

# 6. ASSESSMENT AND FOLLOW-UP

Patients will be followed up according to national and local protocols, looking for local and systemic relapse within the requested funding envelope. We aim for a minimum of 12 months and a maximum of 36 months follow up. We anticipate that follow-up beyond this will become part of routine clinical practice.

# 7. STATISTICs and data analysis

Data and all appropriate documentation will be stored for a minimum of 5 years after the completion of the 36 month study.

The statistical analysis will be undertaken by an experienced statistician ([name]).

Kaplan-Meier survival analysis.

Cox proportional hazard analysis for factors associated with survival.

Genomic quantitative and qualitative data analysis to be undertaken by bioinformaticians and statisticians.

Apart from basic data visualization the data will be subjected to logistic regression analysis with the diagnosis as a categorical outcome variable and the circulating DNA levels (as well as other) as an independent continuous numerical variable. Depending on the result of the initial analysis appropriate threshold levels will be identified and the data will be subjected to Kaplan-Meier Aalen-Johansen survival analysis. The Cox proportional hazards model will be used to examine subsequently if circulating DNA (ctDNA) levels are associated with prognosis. Using sequential monitoring of ctDNA levels, time series will be visualised and analysed using standard prediction techniques and Auto-Regressive Integrated Moving Average (ARIMA) modelling.

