**Measurement of IDH1 mutation**

Droplet digital polymerase chain reaction (ddPCR) is currently the most sensitive and accurate method for detecting and quantifying mutant DNA molecules. We will use the BioRad QX200 ddPCR platform for this study as using this machine we have demonstrated that we can detect the common *IDH1* mutations at below 1 mutant molecule in 10,000 wildtype molecules and quantify mutant molecules across over 4 orders of magnitude (Cancer Medicine in press). We have also optimized the ddPCR assays for the 7 common *IDH1* variants in both formalin-fixed paraffin-embedded tumour and blood samples.

Based on the background error rate of the assay (1 mutant only droplet per ~18,000 wild type droplets), and the average number of molecules we assessed per time point (n=1489), blood samples were deemed to be circulating tumour DNA (ctDNA)-positive if they had a minimum of 2 mutant only droplets.

This process is set up as a standard NHS clinical service with standard operating procedures in an UKAS-accredited histopathology department.

The equipment is serviced annually.

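### Section 7 lets ctDNA thresholds be read off this study's own logistic model of diagnosis and used to split the same patients for survival curves, although an assay-based positivity rule already exists

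*Protocol*

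**What the plan says.** Section 7 sets out a sequence. It starts with "logistic regression analysis with the diagnosis as a categorical outcome variable and the circulating DNA levels", the levels entering "as an independent continuous numerical variable". Next comes the step at issue: "Depending on the result of the initial analysis appropriate threshold levels will be identified and the data will be subjected to Kaplan-Meier" and Aalen-Johansen analysis. Last, a Cox model "will be used to examine subsequently if circulating DNA (ctDNA) levels are associated with prognosis". No threshold is named for the Cox model. Nothing in the protocol mentions a hold-out set, cross-validation or an external cohort for the threshold.

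Elsewhere the protocol thinks in terms of detection. Primary objective 1 (section 2.1) contrasts the prognosis of patients with and without detected pre-operative ctDNA. The first outcome in section 3.3 is pre-operative detection; the other two concern levels. Under Measurement of IDH1 mutation in section 3.1, "blood samples were deemed to be circulating tumour DNA (ctDNA)-positive if they had a minimum of 2 mutant only droplets", on the basis of a background of "1 mutant only droplet per ~18,000 wild type droplets" and an average of 1489 molecules per time point. Section 7 does not refer to that rule.

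**The concern.** A threshold selected on a set of patients and then used to compare those patients will, on average, flatter the comparison. Here selection is against diagnosis, which includes grade, and section 1.1 calls grade the best prognosticator of metastasis and survival. If the chosen cut happens to line up with grade, the ctDNA groups inherit part of grade's survival difference.

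That matters because the stated hypothesis (section 1.1, Recent developments) is that ctDNA in blood is a more sensitive prognostic indicator than histology. A grouping tuned to histology is poorly suited to showing that. It also leaves primary objective 1, a detected/not-detected question, open to being answered with a different and later definition of positive.

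**Working it through.** **No design figure to reproduce.** The protocol states no alpha, power, event count or effect size. The checks below are therefore fresh, with assumptions marked.

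**1. The existing rule.** Treat background droplets as Poisson with mean 1489/18,000 = 0.0827.
- P(at least 2) = 1 − e^(−0.0827)(1 + 0.0827) = 0.0032, about 0.3% per sample.
- P(at least 1) = 1 − e^(−0.0827) = 0.079, about 7.9%.

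The 2-droplet rule is thus a defensible fixed cut that uses no outcome or diagnosis data.

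**2. Patients with ctDNA results.** Plasma is tested only when the tumour carries an IDH1 mutation, about 60%. So 0.6 × 100 = 60 chondrosarcomas and 0.6 × 30 = 18 enchondromas, 78 in all.

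**3. Effect of tuning the cut to diagnosis.** Simulation of 78 patients, 6,000 runs per row, two-sided 5% log-rank comparison, ctDNA unrelated to diagnosis and survival.
- From section 1.1: 5-year survival 81% (GII), 43% (GIII), 10% (dedifferentiated).
- Assumed: 5-year survival 99% (enchondroma) and 95% (GI); grade mix 18/20/24/8/8 in the order enchondroma, GI, GII, GIII, dedifferentiated; 45% positive; log-normal levels among positives; follow-up uniform over 12 to 36 months (the range is from section 6).
- Monthly hazard = −ln(S5)/60, for example −ln(0.81)/60 = 0.0035 for GII; then multiplied by 1, 2 or 3 to vary the number of events.
- Diagnosis-tuned cut: the largest absolute Youden index for high versus low grade, each group holding at least 10% of patients.

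| Hazard multiplier | Mean events | Fixed detected/not detected | Cut tuned to diagnosis |
|---|---|---|---|
| 1 | 9.3 | 4.8% | 6.0% |
| 2 | 15.1 | 4.8% | 8.7% |
| 3 | 19.0 | 4.7% | 9.0% |

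The Monte Carlo standard error is at most √(0.09 × 0.91/6000) = 0.4 percentage points. A separate simulation of the same procedure, also with assumed grade mix and survival, gave about 7 to 10%. The working range is therefore about 6 to 10%.

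**4. Can the logistic step fail?** Section 1.1 reports 0 of 8 enchondroma/GI patients positive, 7 of 14 GII positive, and 14 GIII/dedifferentiated patients positive with no clear denominator. (The groups as worded add to 8 + 14 + 14 = 36, against 30 stated; both readings were tried.) All positives are high grade, but 7 GII patients share the zero value with the low-grade group, so low versus high grade is quasi-completely separated.
- In data of that shape the slope for detected/not detected grows without limit: 6.3, 11.3, 16.3, 21.3, 26.3 and 31.3 at iterations 5, 10, 15, 20, 25 and 30. The slope on log level also diverges.
- Adding one low-grade positive makes the log-level slope finite: 1.15 under the 36-patient reading, 1.01 under the 30-patient reading.
- 0/8 bounds the low-grade positive rate only below 1 − 0.05^(1/8) = 31% (one-sided 95%) or 1 − 0.025^(1/8) = 37% (two-sided).
- P(no positive among 18 enchondromas) = (1 − p)^18: 94% at p = 0.3%, 40% at 5%, 15% at 10%, 2% at 20%. With 38 low-grade patients (20 GI assumed): 88%, 14%, 2% and about 0%.

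**The case against.** Several points on the other side stand.

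- The Cox model already uses ctDNA levels, so that prognostic analysis does not depend on the threshold. No test is named for the Kaplan-Meier step; the log-rank comparison above is my assumption.
- The 2-droplet rule is an assay-calling rule worded in the past tense, while the thresholds in section 7 concern magnitude, and section 3.3 lists both detection and levels. The two can coexist. What is missing is a statement of which one answers primary objective 1.
- If no low-grade patient is positive, the best cut for low versus high grade is the lowest positive value, which is simply detection. In that case the derived threshold largely collapses onto the fixed rule.
- The statistical analysis plan is not shown, and the validation method, transformation of levels and penalised fitting normally belong there. However, the protocol itself commits to a threshold that depends on the initial result, so an analysis plan that fixed the cut in advance would depart from it.

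Two stronger readings are tempting. A reader might infer the heavy inflation of a minimum-p cut-point. In the same simulation, a cut chosen for the smallest survival p-value gave 21 to 23% false positives. But section 7 derives thresholds from a model with "logistic regression analysis with the diagnosis as a categorical outcome variable", not from survival, so that figure does not describe this plan. A reader might also infer from the pilot that the logistic model is bound to separate. Eight low-grade patients cannot establish that.

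**Conclusion.** The point holds in a limited form. Section 7 permits a diagnosis-tuned, unvalidated threshold to define the survival groups, although a fixed assay-based rule exists and the primary question is about detection. The optimism is mild: about 6 to 10% false positives at a nominal 5%, against about 5% for the fixed rule. This rests on the assumed grade mix, low-grade survival, 45% positive rate and log-rank comparison, and on the Youden index as one plausible reading of how the threshold would be picked. The larger cost is interpretive: the groups are pulled towards histology, the very standard that ctDNA is meant to improve on. A non-finite logistic estimate is a real possibility but not a prediction.

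**What to change.** In section 7, state that the rule of at least 2 mutant-only droplets, expressly adopted for this study, defines the primary Kaplan-Meier and Aalen-Johansen groups. Keep ctDNA level continuous in the Cox model, as already planned. Label any threshold derived from the study's data exploratory and report it with internal validation. A penalised (Firth) logistic fit is a sensible fallback if no low-grade patient is positive; this can be left to the statistical analysis plan.

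The cost is a few sentences in section 7 and one in section 3.1 adopting the rule. It has to be done before outcomes are examined, because a cut cannot be pre-specified afterwards. The downside is that the curves may separate less. The fixed rule removes the tuning; it does not by itself show that ctDNA adds to grade.

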**Recent developments**

We were the first to show that *IDH1* mutations are detected in ~60% of conventional central chondrosarcomas and enchondromas (Amary *et al*). It is now known that the presence of *IDH1* mutations in the tumour neither affects the prognosis nor the clinical management of the patient.

We then investigated in a proof of concept study (in press Cancer Medicine) involving 30 patients if *IDH1* mutations can also be found in the blood , that is, as circulating tumour DNA (ctDNA). We found that 14 patients with GIII and dedifferentiated chondrosarcoma, and 50% of patients with GII chondrosarcoma (7 out of 14 patients) had measurable levels of mutant copies in their blood. Of note is that no circulating tumour DNA was identified in the blood of 8 patients with either an enchondroma or GI chondrosarcoma.

Based on our results **we hypothesise** that the detection of mutant *IDH1* in the blood is a more sensitive prognostic indicator for chondrosarcoma than histology.

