# 2. STUDY OBJECTIVES

## 2.1 PRIMARY AIM

1. We aim to provide a more accurate and highly reproducible prognosis for patients with chondrosarcoma by evaluating a biomarker which is present in the majority of conventional central cartilaginous tumours (enchondroma and chondrosarcoma).

PRIMARY OBJECTIVES

1. Does detection of pre-operative ctDNA indicate a poorer prognosis than if not detected?
2. Does detection of post-surgery ctDNA predict tumour relapse?
3. Does ctDNA detection after surgery indicate residual and or metastatic disease?

iii) Can ctDNA in conjunction with imaging allow diagnosis of chondrosarcoma without a biopsy?

iv) Can correlation of ctDNA with histology reduce the variation in grading of cartilaginous tumours provided by histopathologists?

v) Can correlation of ctDNA with imaging reduce the variation in grading of cartilaginous tumours provided by radiologists?

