## 3.3 Study outcome measurements

1. Detection of *IDH1* ctDNA pre-operatively
2. Levels of the *IDH1* ctDNA after surgery
3. Correlation of ctDNA levels with histology, radiology and clinical behaviour of tumour

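### Primary objective 1 asks about ctDNA detection, but section 7 analyses ctDNA levels, leaves their scale in the Cox model open and never uses the positivity rule the protocol already defines

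*Protocol*

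**What the plan says.** Protocol section 2.1 states the first primary objective as a binary question: "Does detection of pre-operative ctDNA indicate a poorer prognosis than if not detected". Section 3.3 lists "Detection of *IDH1* ctDNA pre-operatively" as its first outcome measure. Section 3.1 (Measurement of IDH1 mutation) fixes when a blood sample counts as positive: at least two mutant-only droplets.

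Section 7 takes a different route, in three steps:

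- A logistic regression with diagnosis as outcome takes "the circulating DNA levels (as well as other) as an independent continuous numerical variable".
- Cut-offs are then chosen in the light of that first result, and patients are compared by Kaplan-Meier/Aalen-Johansen curves.
- Last comes the prognostic model, described in one sentence: "The Cox proportional hazards model will be used to examine subsequently if circulating DNA (ctDNA) levels are associated with prognosis".

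Section 7 also has a general line on Cox analysis of factors associated with survival, without naming the factors. It does not mention detected versus not detected, or the two-droplet rule.

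**The concern.** The objective and the analysis concern different quantities. Someone who follows section 7 step by step reports a logistic coefficient per unit of level, survival curves split at a cut-off found in the same data, and a Cox coefficient for level. None of these is necessarily the hazard ratio for detected versus undetected that objective 1 calls for.

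The shape of the variable makes this matter. Many samples will be zero, and the positive ones may be strongly skewed. On an untransformed linear scale, the step from 0 to 10 copies counts 1,000 times less than the step from 10,000 to 20,000. Undetected patients and patients with low positive values then look almost identical to the model, and a few extreme samples set the coefficient. With events likely to be few, a real difference by detection status could be missed.

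**Working it through.** The protocol gives no power, event count or ctDNA distribution, so there is no figure of its own to reproduce.

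**Share undetected (section 1.1, Recent developments).** The pilot found ctDNA in 7 of 14 GII patients, and "no circulating tumour DNA was identified in the blood of 8 patients with either an enchondroma or GI chondrosarcoma". Undetected: 7 + 8 = 15. The listed groups add up to 14 + 14 + 8 = 36, although the text says 30 patients. The share is 15/36 = 42% on the listed groups. On 30 patients it is 15/30 = 50%, or 16/30 = 53% if 14 is read as the total number positive. The trial's grade mix may differ.

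**Patients with testable plasma.** About 60% of tumours carry the mutation (section 1.2), and only those patients' plasma is tested (section 3.1): 0.6 × 100 = 60 chondrosarcomas.

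**Hazards (assumed, from the 5-year survival figures in section 1.1).** Undetected patients take the GII figure: −ln(0.81)/5 = 0.042 per year. Detected patients take the GIII figure: −ln(0.43)/5 = 0.169 per year. The ratio is 4.0.

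**Expected events.** With censoring uniform over 1 to 3 years (section 6 gives 12 to 36 months), P(event) = 1 − (e^−λ − e^−3λ)/(2λ). This is 0.081 for undetected and 0.283 for detected patients. With 30 in each group: 30 × 0.081 + 30 × 0.283 = 10.9.

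**Simulated power.** Univariable Cox models, likelihood-ratio test, two-sided 5% (assumed). Levels among detected patients are assumed log-uniform from 2 to 20,000 copies. Ranges cover separate simulations of the same set-up; a dash means not reported.

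| Truth (n = 60) | Raw level | Detected yes/no | log10(1 + level) |
|---|---|---|---|
| Detection only, HR 4.0, about 11 events | 11–12% | 56–58% | 35% |
| Same, upper level cut to 1,489 copies | 14% | 58–60% | – |
| Same, hazards doubled, about 19 events | 17% | 80% | – |
| HR 1.6 per log10 of level, about 10 events | 35–36% | 38–43% | 57–62% |
| Same, hazards doubled, about 17 events | 53–54% | 62% | 81% |
| No effect | 8% | 5% | 5–6% |

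When risk rises per log10 of level, detection gains 38 − 35 = 3, 43 − 36 = 7 or 62 − 53 = 9 points over raw. The log10 scale gains 57 − 35 = 22, 62 − 36 = 26 or 81 − 53 = 28 points.

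**Second set of assumptions.** Here 10% of undetected patients have an event by 24 months, and n = 60.

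- Detection effect only, HR 3: raw 10%, detected 42%. HR 5: raw 14–16%, detected 79–81%.
- Levels spread over only 2 or 3 decades, HR 3: raw 10–11%, detected 39–40%.
- HR 3 at mid-range plus a log-hazard slope of 0.5 per decade: raw 44%, detected 48%, log10 69%.
- The same with a slope of 1.0 per decade: raw 87%, detected 67%, log10 95%.

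**Influence on the raw scale (detection effect only, 4 decades, n = 60 or 78).** The five highest values carry about 80–89% of the covariate's sum of squares. Dropping the single highest value changes the coefficient by a median of 62–78%. A true hazard ratio of 3 to 5 appears as about 1.01 at the median detected level.

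**The case against.** A reader might infer that the protocol commits the Cox model to an untransformed level. It does not. The phrase about a continuous numerical variable belongs to the logistic model, and a log-transformed level is continuous too. The Cox sentence follows the threshold step and gives no scale, so a raw, log or cut covariate all fit it. Transformation and coding are often left to a statistical analysis plan, which is not at hand. This stands, so the dominance of a few values and the power loss are risks if the raw level is used, not established consequences.

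Three other tempting readings also fail:

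- That patient values span four decades. The words "quantify mutant molecules across over 4 orders of magnitude" describe the assay's range, not the spread in patients. The raw-scale loss does not depend on it: it persists at 2 to 3 decades and with the upper level cut to 1,489 copies.
- That Cox on levels is the only prognostic regression. The general Cox line would allow a detection term, and the Kaplan-Meier/Aalen-Johansen step keeps some categorical comparison. However, the first does not name detection, and the second uses a cut-off that need not equal the two-droplet rule.
- That a detection term brings a large gain whatever the truth. When risk rises with log level its gain over raw is small, and with a steep dose-response raw level does better than detection alone.

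The mismatch remains. Section 7 does more than stay silent: it sets out a sequence built on levels and data-derived cuts, while the objective, the first outcome measure and the positivity rule all concern detection.

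**Conclusion.** The point holds as a mismatch between objective and analysis, with a conditional loss of power. Section 7 as written does not name the contrast in primary objective 1 and does not use the rule that defines it.

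If the level were entered raw and hazard depended on detection only, power would be about 12% against about 58% for detected yes/no. That rests on 60 patients, half of them detected, a hazard ratio of 4, about 11 events and a log-uniform spread of levels. All but the patient count are assumptions or follow from them. The size of the loss depends on the dose-response, so no single gain can be promised. In every scenario where it was reported, the log10 scale beat raw level, by 8 points (95 against 87) in the steepest case. It is not a substitute for detection in objective 1: when hazard depended on detection only, log10 level reached 35% against 56–58%.

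The change is worth making because it is nearly free and gives objective 1 a defined test.

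**What to change.** In section 7, state that:

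1. Objective 1 is tested by the Cox coefficient for pre-operative ctDNA detected yes/no, under the existing rule of at least two mutant-only droplets, in a model without level.
2. Where level is used in the Cox or logistic models, it enters as log10(level) among detected patients (0 if undetected) alongside the detection indicator, as a secondary analysis. State the unit of level.

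The test in item 1 should come from the model without level. Once log10 level is added, the detection coefficient describes a patient at a level of one unit, so it changes with the unit chosen.

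Cost: a sentence or two of wording, with no new patients, samples or assays. The downside is one extra model term when level is added, which is a real price with few events; this is why the single detection term carries objective 1. If the pilot pattern repeats and no low-grade patient is positive, a logistic model separating low from high grade has no finite ordinary estimate for the ctDNA term. That is true of raw level as well, so it is not a cost of this change.
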